# Large-scale (Phase III) evaluation of broflanilide 50WP (VECTRON™ T500) for indoor residual spraying for malaria vector control in Northeast Tanzania: study protocol for a two-arm, non-inferiority, cluster-randomised community trial

**DOI:** 10.1186/s12879-022-07138-3

**Published:** 2022-02-21

**Keywords:** Insecticide resistance, Broflanilide, Clothianidin, Indoor residual spraying, Vector density, Entomological inoculation rate

## Abstract

**Background:**

Indoor residual spraying (IRS) is a major method of malaria vector control across sub-Saharan Africa. Effective control is being undermined by the rapid spread of insecticide resistance. There is major investment in development of new insecticides for IRS that possess novel modes of action, long residual activity, low mammalian toxicity and minimal cross-resistance. VECTRON™ T500, a new IRS product containing the active ingredient broflanilide as a 50% wettable powder (WP), has been shown to be efficacious against pyrethroid susceptible and resistant vector species on mud and concrete substrates in experimental hut (Phase II) trials.

**Methods:**

A two-arm non-inferiority cluster randomized controlled trial (Phase III) will be undertaken in Muheza District, Tanga Region, Tanzania. VECTRON™ T500 will be compared to the IRS product Fludora® Fusion (clothianidin 50% WP + deltamethrin 6.25% WP). The predominant malaria vectors in the study area are pyrethroid-resistant *Anopheles gambiae s.s.*, *An. arabiensis* and *An. funestus s.s*. Sixteen village clusters will be pair-matched on baseline vector densities and allocated to reference and intervention arms. Consenting households in the intervention arm will be sprayed with VECTRON™ T500 and those in the reference arm will be sprayed with Fludora® Fusion. Each month, CDC light traps will collect mosquitoes to estimate changes in vector density, indoor biting, sporozoite and entomological inoculation rates (EIR). Susceptibility to IRS active ingredients will be assessed using World Health Organisation (WHO) bottle bioassays. Target site and metabolic resistance mechanisms will be characterised among *Anopheles* field populations from both trial arms. Residual efficacy of both IRS products will be monitored for 12 months post intervention. Questionnaire and focus group discussions will explore factors that influence adherence, adverse effects and benefits of IRS.

**Discussion:**

This protocol describes a large-scale non-inferiority evaluation of a novel IRS product to reduce the density and EIR of pyrethroid-resistant *Anopheles* vectors. If VECTRON™ T500 proves non-inferior to Fludora® Fusion, it will be considered as an additional vector control product for malaria prevention and insecticide resistance management.

*Trial registration:* ClinicalTrials.gov, NCT05150808, registered on 26 November 2021. Retrospectively registered.

## Background

Vector control is an essential component of all malaria control strategies [1], with long-lasting insecticidal net (LLIN) distribution and indoor residual spraying (IRS) contributing 68% and 13%, respectively, to the estimated decline in malaria cases between 2000 and 2015 [2]. In 2019, about 253 million LLINs were delivered globally by manufacturers to malaria endemic countries and out of these, 84% were delivered to countries in sub-Saharan Africa [3]. While the provision of LLINs to endemic countries in sub-Saharan Africa increased from 145 million in 2010 to about 213 million in 2019; there has been a decline in the percentage of the population at risk protected by IRS in sub-Saharan Africa from 10.1 to 5.7% and globally from 5 to 2% during the same period [3]. The decline in IRS coverage has been attributed to the development of insecticide resistance, lack of inexpensive alternative insecticides and limited resources for annual applications of the intervention [4].

Scientific evidence of the efficacy of IRS in reducing or interrupting malaria transmission in different epidemiological settings has been available since the 1950–60s [5]. IRS is effective in controlling malaria transmission and in reducing related morbidity and mortality, provided the majority of premises within targeted communities are treated [6]. The application of IRS products consistently over time in large areas has altered the vector distribution and, subsequently, the epidemiological pattern of malaria in several African countries, including Botswana, Namibia, South Africa, eSwatini and Zimbabwe, significantly reducing major vectors of malaria, *Anopheles funestus* and *An. gambiae* sensu stricto [7]. Between 2006 and 2010, pyrethroid IRS product use was scaled up in sub-Saharan Africa mainly due to their affordability and relatively long residual effect [4]. However, development and spread of multiple mechanisms of pyrethroid resistance, including knockdown resistance mutations L1014F (kdr West) and L1014S (kdr East), across Africa poses a serious challenge to pyrethroid IRS control of malaria vectors [8]. For example, operational failure of deltamethrin IRS campaigns in South Africa was attributed to insecticide resistance observed in the malaria vector *An. funestus* [9, 10]. Similarly, the development and spread of pyrethroid resistance in *An. gambiae* [8, 9] in Equatorial Guinea and island of Bioko reduced the efficacy of IRS and LLINs [11, 12]. Mutations in the voltage-gated sodium channels, combined with metabolic resistance through overexpressed mixed function oxidase enzymes, gave clear survival advantages to their mosquito carriers [8, 13]. This necessitated the development and introduction of IRS formulations with more costly insecticides from the carbamate and organophosphate chemical classes that have a different mode of action to pyrethroids [4]. Despite the carbamate bendiocarb being highly effective, the formulated IRS product has a short residual duration, with the consequence that multiple spraying cycles are required in areas with long transmission seasons for maximum effect [4, 14]. The organophosphate pirimiphos-methyl formulated as a microcapsule suspension has shown residual duration of up to 12 months [4, 15, 16]. However, target site mutations and copy number variants have evolved in the acetylcholinesterase gene (Ace-1) that confer cross-resistance to both carbamates and organophosphates [17]. Between 2010 and 2019, resistance to carbamates and organophosphates has been detected respectively in 31.7% and 24.9% of sites that reported monitoring malaria vector resistance status [3].

The Global Plan for Insecticide Resistance Management (GPIRM) published by the WHO proposed among other things, the development of new active ingredients (AIs) with different modes of action which could be used in strategies to manage insecticide resistance [1]. These resistance management schemes are primarily based on IRS and include the use of rotations and mixtures of insecticides from different classes. Recently, IRS formulations have been developed which contain the neonicotinoid insecticide clothianidin, either as a single AI in SumiShield™ 50 WG or as a mixture with deltamethrin in Fludora® Fusion; bringing the total number of insecticide classes for IRS on the World Health Organization (WHO) Prequalification Vector Control Product Assessment Team (WHO PQT/VCP) list to four (carbamate, organophosphate, pyrethroid and neonicotinoid) [18, 19]. With IRS playing the main role in strategies for insecticide resistance management, there is a need to develop further active ingredients with new modes of action.

VECTRON™ T500, a newly developed IRS product by Mitsui Chemicals Agro, Inc. (Tokyo, Japan) has been shown to be efficacious against both pyrethroid-susceptible and -resistant mosquito species [20]. The active ingredient in VECTRON™ T500 is broflanilide, a meta-diamide *N*-[2-bromo-4-(perfluoropropan-2-yl)-6-(trifluoromethyl)phenyl]-2-fluoro-3-(*N*-methylbenzamido)benzamide] insecticide, which has a mode of action different to other insecticide classes [21]. Broflanilide is classified by the Insecticide Resistance Action Committee (IRAC) in the new class 30; GABA-gated chloride channel allosteric modulators [21, 22]. In 2021, VECTRON™ T500 demonstrated prolonged effectiveness in small-scale experimental hut trials (Phase II) against WHO Prequalified products in Tanzania and Benin [20].

For VECTRON™ T500 to be recommended by WHO PQT/VCP as a new IRS product, it must demonstrate superior or equivalent efficacy to a currently recommended WHO PQT/VCP listed IRS product in a non-inferiority community-level trial with entomological endpoints [23].

## Study objectives

### Primary objective

To determine non-inferiority of VECTRON™ T500 to the reference product Fludora® Fusion (Bayer AG, Monheim, Germany), which has been prequalified by WHO PQT/VCP, in reducing vector population density. This will be determined by the difference between the number of female *An. gambiae* sensu lato, *An. funestus s.l.* and *Culex* spp*.* caught per trap night in clusters sprayed with VECTRON™ T500 compared to Fludora® Fusion. Individuals from morphologically identical species complexes will be identified to species level using molecular diagnostics.

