### Secondary objectives

To assess the duration of residual efficacy of VECTRON™ T500 on mud and concrete sprayed wall surfaces during the 12-month post-intervention period.To determine seasonal sporozoite rate and entomological inoculation rates (EIRs) of vectors, and the number of *Plasmodium falciparum* infective bites received per person during the post-intervention period.To record the difference between the number of female *Culex* spp*.* caught per trap night in clusters sprayed with VECTRON™ T500 compared to Fludora® Fusion.To assess the resistance status of wild *Anopheles* and *Culex* spp. populations to any of the insecticides being used during the post-intervention period.

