### Power calculation, estimation of effect size and cluster selection

Sample size calculations will be based on the study primary endpoint i.e., indoor density of *Anopheles* mosquitoes. An estimated mean of 3.0 female *Anopheles* per light trap per night will be used, referencing data from recent studies in Tanzania [27]. A paired design will be used in which clusters will be matched on baseline indoor density of *Anopheles* mosquitoes. Previous data suggests a within-pair coefficient of variation of 0.23, but a conservative value of 0.3 will be used in our calculations.

The trial is a non-inferiority design, intended to show that spraying the intervention product, VECTRON™ T500, will not result in higher malaria vector densities, by a prespecified non-inferiority margin of 50%, than those per trap per night in the reference arm sprayed with Fludora® Fusion. Using the methods described in Hayes and Moulton [28] and the assumptions listed above, it was calculated that 8 clusters per treatment arm (16 in total) will be needed for the 50% margin to have 80% power to demonstrate non-inferiority. The calculations were based on 49 trap nights per cluster. There was very limited statistical advantage in increasing trap-nights beyond 50. This number of clusters considers the loss of degrees of freedom caused by matching.

Sixteen clusters, containing 75–200 households per cluster (HHs), will be selected for spraying. Core areas of clusters should be at least 1 km apart to prevent infiltration of mosquitoes from other villages. All consenting HHs in all 16 clusters will be sprayed. Approximately 1200–3200 households will be sprayed (~ 75–200 HHs/cluster in 16 clusters).

Although a minimum of 49 households is required per cluster according to the sample size calculations, a larger hamlet will be recruited for logistical reasons, as a proportion of households may refuse to accept the IRS spraying and others may be absent during spraying or lost during follow-up.

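### The primary endpoint is defined inconsistently: the primary objective counts Culex, while the sample size, matching and margin are set on Anopheles or malaria vectors only

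*Protocol article*

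**What the plan says.** Four places in the protocol article bear on which mosquitoes count.

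- **Primary objective.** The aim is non-inferiority "in reducing vector population density". The measure is the catch of female An. gambiae s.l., "An. funestus s.l.* and *Culex* spp*.* caught per trap night in clusters sprayed with VECTRON™ T500" against clusters sprayed with the reference product.
- **Secondary objectives.** One item reads "To record the difference between the number of female *Culex* spp*.* caught per trap night", with the same two products compared.
- **The power calculation section.** It opens by naming the endpoint: "Sample size calculations will be based on the study primary endpoint i.e., indoor density of *Anopheles* mosquitoes". The inputs follow suit: "An estimated mean of 3.0 female *Anopheles* per light trap per night will be used", and "clusters will be matched on baseline indoor density of *Anopheles* mosquitoes". The trial is to show that the new product "will not result in higher malaria vector densities, by a prespecified non-inferiority margin of 50" per cent.
- **Data analysis.** The primary endpoint is called mosquito density, with no species named. It is analysed as a ratio within each matched pair, with a paired t-test.

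The section on study area and cluster selection lists only Anopheles species as the main malaria vectors in the district.

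**The concern.** Culex is in the primary comparison by one section, outside it by another, and secondary by a third. The analysis section uses a term that fits either definition. Once the data are in, someone could choose between an Anopheles count and a count that includes Culex, and each choice could be defended from the text.

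The choice matters because this is a non-inferiority test. A component that does not differ between arms moves a pooled ratio towards 1, which makes non-inferiority easier to declare. The background section ties the result to a WHO prequalification recommendation, so the claim about malaria vectors should rest on a count of malaria vectors. The mean, coefficient of variation and margin behind the sample size were also not set for a count that includes Culex.

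**Working it through.** **1. Does the stated sample size belong to Anopheles?**

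Inputs from the power section: mean λ₀ = 3.0 Anopheles per trap night, within-pair coefficient of variation k = 0.30, y = 49 trap nights per cluster, 80% power, margin 50%. On a mean of 3.0 the margin is d = 1.5. The significance level is not stated; two-sided 0.05 is assumed. The true ratio is taken as 1, so λ₁ = λ₀.

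Matched-pair formula for rates:

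c = 2 + (z_α + z_β)² × [(λ₀ + λ₁)/y + k²(λ₀² + λ₁²)] / d²

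- (1.960 + 0.842)² = 7.85
- (3 + 3)/49 + 0.09 × (9 + 9) = 0.122 + 1.620 = 1.742
- 1.742 / 2.25 = 0.774
- c = 2 + 7.85 × 0.774 = 8.08

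Power at 8 per arm is 79.5%, so the stated figure is reproduced. One-sided 0.05 would give 6.79. The article gives no Culex mean, coefficient of variation or margin, so no such calculation can be made for a count that includes Culex.

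**2. What would pooling do to the ratio?**

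This step needs assumptions that the article does not supply: the taxa are summed, Culex has the same mean C per trap night in both arms, and C takes a range of values. With true Anopheles ratio R:

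pooled ratio = (3R + C) / (3 + C)

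| R | C = 1 | C = 3 | C = 6 | C = 10 | C = 30 |
|---|---|---|---|---|---|
| 1.5 | 1.38 | 1.25 | 1.17 | 1.12 | 1.05 |
| 2.0 | 1.75 | 1.50 | 1.33 | 1.23 | 1.09 |

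For example, R = 2.0 and C = 6 gives (6 + 6)/(3 + 6) = 1.33. A true Anopheles ratio of 2.0 falls below 1.5 only once C exceeds 3.

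**3. What would pooling do to the error rate?**

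A pooled ratio below 1.5 is not itself a declaration of non-inferiority; the upper confidence limit must be below 1.5. This was simulated with 8 pairs, 49 trap nights per cluster, coefficient of variation 0.3 for each taxon, a paired t-test on log ratios, and one-sided 0.025 (assumed). Each range runs from fully shared to independent variation of the taxa between clusters.

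| True Anopheles ratio | No Culex | C = 3 | C = 6 | C = 10 |
|---|---|---|---|---|
| 1.5 (at the margin) | about 2% | 17–29% | 29–48% | 38–56% |
| 2.0 | 0% | about 3% | 10–14% | 20–29% |

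**4. If the taxa are tested separately.** No dilution arises. The primary objective then holds a Culex test with no stated margin or power.

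**The case against.** The best defence is that the Culex wording is a slip in one sentence. The power section defines the endpoint as Anopheles and matches on it. The abstract's discussion and the main Discussion speak of Anopheles or malaria vectors, and a separate Culex objective would be redundant if Culex were meant as primary. This is the likeliest reading, and it supports the fix below. It does not remove the conflict, because the sentence in question is the one that says how non-inferiority will be determined, and the Data analysis section does not correct it.

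A reader might infer that a Culex population unaffected by the products will carry an inferior product through. The documents do not support that:

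- Nowhere are the three taxa said to be summed. The vector density section lists them as separate categories.
- Nothing says that Culex is unaffected by either product or responds equally to both. If it responds differently, the bias could go either way.
- No Culex density is given. With few Culex the dilution is small: at a true Anopheles ratio of 1.8 and C = 1, the pooled ratio is (5.4 + 1)/4 = 1.60, still above the margin.
- Even with dilution the inferior product often fails. At a true ratio of 1.8, non-inferiority is declared in about 6–8% of trials at C = 3, 16–25% at C = 6 and 24–37% at C = 9.

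These objections limit the consequence. They leave the contradiction untouched.

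**Conclusion.** The primary endpoint is stated in incompatible ways, and the text available does not settle which applies. This rests on the wording alone and needs no assumption. The stated 8 clusters per arm belongs to the Anopheles definition, so it remains adequate on the protocol's own terms if Culex is removed, and the stated power does not carry over if Culex is included.

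The inflation of false non-inferiority at a true Anopheles ratio of 1.5 is conditional. It requires summed taxa, equal Culex response, a Culex mean of the assumed size, and the assumed significance level. Under those conditions it is large enough to undermine the primary conclusion. Under separate testing it is absent, but the Culex test then lacks a margin and power. Each reading needs a correction to the text, and the point should be settled before the primary analysis.

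**What to change.** - In the primary objective, delete Culex. State the primary endpoint as total female An. gambiae s.l. plus An. funestus s.l. per trap night over the 12 months after spraying, with a non-inferiority margin of ratio 1.5.
- In the Data analysis section, replace mosquito density with Anopheles density.
- Keep Culex only as the secondary outcome already listed.
- Carry the same definition into the analysis plan.

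The cost is a few words in two sections. Trapping, identification and sample size stay as they are, and Culex is still counted and reported.

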### Secondary objectives

To assess the duration of residual efficacy of VECTRON™ T500 on mud and concrete sprayed wall surfaces during the 12-month post-intervention period.To determine seasonal sporozoite rate and entomological inoculation rates (EIRs) of vectors, and the number of *Plasmodium falciparum* infective bites received per person during the post-intervention period.To record the difference between the number of female *Culex* spp*.* caught per trap night in clusters sprayed with VECTRON™ T500 compared to Fludora® Fusion.To assess the resistance status of wild *Anopheles* and *Culex* spp. populations to any of the insecticides being used during the post-intervention period.

### Tertiary objectives

To determine the quality of the IRS applications.To record adverse events among spray teams and treated households.To assess community acceptability of VECTRON™ T500.

## Methods/designs

### Study area and cluster selection

This study will be carried out in Muheza District, Tanga Region, Northeast Tanzania (Fig. 1). The population of Muheza District consists primarily of subsistence farmers [24]. The region has a tropical climate with a long rainy season from March to June and a short rainy season from October to December. Most houses within Muheza District are constructed from mud or cement with a thatched or iron roof. In 2012, surveys conducted in Muheza District found that 83% of households owned at least one ITN (insecticide-treated net), and there have been two LLIN distribution campaigns carried out since then [25]. Malaria transmission occurs all year round with two peaks in transmission following the two rainy seasons. The main malaria vectors in Muheza District are *An. gambiae* s.s., *An. arabiensis* and *An. funestus* s.s. [25]*.* Wild *An. gambiae* s.l. from Muheza District are resistant to pyrethroids [26].

**Fig. 1 Fig1:**
[figure not shown]
Study area **A** location of Muheza District in Northeast Tanzania; **B** proposed clusters in Muheza District. The maps of Tanzania and Muheza district were produced using QGIS 3.22 software [44] and overlaid on Google Earth satellite images by the study investigator ([name]). Using QGIS 3.22 software [44], a one kilometre transect from the mid-point to the perimeter of each village was digitized to produce the shape files for the clusters in the Muheza map

### Study design

A matched cluster randomized controlled non-inferiority study design will be used as IRS in community-level intervention. The study monitoring period will be for 12 months post-intervention or beyond this date if residual efficacy on house walls indicates continuing effectiveness. Baseline data collection on vector densities will commence in the six months preceding the randomisation and pair matching of the clusters. At the onset of the long rainy season, one round of IRS will be done which will be followed by monthly vector density monitoring and *in-situ* cone bioassays. Baseline household enumeration and social-cultural and acceptability measurements will be conducted before IRS.

### Power calculation, estimation of effect size and cluster selection

Sample size calculations will be based on the study primary endpoint i.e., indoor density of *Anopheles* mosquitoes. An estimated mean of 3.0 female *Anopheles* per light trap per night will be used, referencing data from recent studies in Tanzania [27]. A paired design will be used in which clusters will be matched on baseline indoor density of *Anopheles* mosquitoes. Previous data suggests a within-pair coefficient of variation of 0.23, but a conservative value of 0.3 will be used in our calculations.

The trial is a non-inferiority design, intended to show that spraying the intervention product, VECTRON™ T500, will not result in higher malaria vector densities, by a prespecified non-inferiority margin of 50%, than those per trap per night in the reference arm sprayed with Fludora® Fusion. Using the methods described in Hayes and Moulton [28] and the assumptions listed above, it was calculated that 8 clusters per treatment arm (16 in total) will be needed for the 50% margin to have 80% power to demonstrate non-inferiority. The calculations were based on 49 trap nights per cluster. There was very limited statistical advantage in increasing trap-nights beyond 50. This number of clusters considers the loss of degrees of freedom caused by matching.

Sixteen clusters, containing 75–200 households per cluster (HHs), will be selected for spraying. Core areas of clusters should be at least 1 km apart to prevent infiltration of mosquitoes from other villages. All consenting HHs in all 16 clusters will be sprayed. Approximately 1200–3200 households will be sprayed (~ 75–200 HHs/cluster in 16 clusters).

Although a minimum of 49 households is required per cluster according to the sample size calculations, a larger hamlet will be recruited for logistical reasons, as a proportion of households may refuse to accept the IRS spraying and others may be absent during spraying or lost during follow-up.

During baseline vector density monitoring, 20 clusters will be included, to improve the pair-matching post-intervention. The four clusters with greatest variance will not be included in the post-intervention monitoring but will still receive the IRS treatment. The 16 selected clusters will be pair-matched based on vector densities and randomly allocated to the two trial arms: one arm (8 clusters) will be sprayed with the novel intervention (VECTRON™ T500) and the other arm (8 clusters), the reference product (Fludora® Fusion). All possible randomisations will be stratified on ITN coverage and wall surface to ensure minimum difference of 15% or less in mean ITN coverage and mean ratio of cement houses to mud houses per arm. From all randomisations that meet these criteria, one will be selected at random.

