### Intervention monitoring

#### Vector density

CDC light traps hung inside houses next to occupied LLINs will be used to collect mosquitoes for species identification, sporozoite ELISA, and characterization of DNA-based resistance mechanisms. Four operatives will be allocated with 5 light traps each and given responsibility for trapping in 4 of the 16 clusters. In each cluster in each month there will be 3 rounds of light trap collections spaced over 3 weeks in 15 randomly selected HHs. Therefore, in each treatment arm of 8 clusters there will be 120 light trap nights in each month. All households in each cluster will be re-randomised at each monthly surveillance point. Therefore, in each cluster there will be 180 light-trap nights spread across the 12-month post intervention period, from which non-inferiority will be determined. All mosquitoes collected will be identified morphologically to genus and species complex level (*An. gambiae s.l.*, *An. funestus s.l.* and *Culex* spp.). Sub-samples taken from each cluster each month will be identified to species level using molecular diagnostic assays; numbers and proportions identified will depend on the total numbers caught.

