### Data analysis

Data analysis will be carried out using NVivo software for qualitative data and Stata (Version 16) for quantitative data. For the FGD data, emerging themes will be assessed using the NVivo software. Count and binary data will be analysed using Generalised Linear Models. Data analysis will be carried out using cluster level summaries since random effects models perform poorly in a matched design with fewer than 20 clusters per arm [28]. For the primary endpoint of mosquito density, the ratio of densities in each matched pair will be calculated and inference will be based on a paired *t*-test. Adjustment will be made for time post-spraying, LLIN use and wall type using the two-stage method described by Hayes and Moulton [28]. The secondary outcomes of EIR, sporozoite rate, estimated number of infective bites per person per year, and residual bioefficacy will be analysed in the same way.

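### The stated 80% power with 8 pairs at CV 0.3 holds for a fixed absolute margin, not for the planned within-pair ratio test, which has about 61% (one-sided 2.5%) or 76% (one-sided 5%)

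*Protocol article*

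**What the plan says.** Under Power calculation, estimation of effect size and cluster selection, the protocol article gives these inputs:

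- Density: "An estimated mean of 3.0 female *Anopheles* per light trap per night will be used".
- Between-cluster variation: "Previous data suggests a within-pair coefficient of variation of 0.23, but a conservative value of 0.3 will be used in our calculations".
- Margin: the new product's densities should not exceed, "by a prespecified non-inferiority margin of 50%, than those per trap per night in the reference arm".
- Sampling: "The calculations were based on 49 trap nights per cluster".
- Result: "8 clusters per treatment arm (16 in total) will be needed for the 50% margin to have 80% power to demonstrate non-inferiority". The section cites Hayes and Moulton and says the loss of degrees of freedom from matching has been allowed for.

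No significance level, sidedness or analysis scale is given for this calculation.

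Under Data analysis, the primary test is specified on the ratio scale: "the ratio of densities in each matched pair will be calculated and inference will be based on a paired *t*-test". Under Vector density, the sampling actually planned is larger than in the calculation: "in each cluster there will be 180 light-trap nights spread across the 12-month post intervention period". The primary objective speaks of a difference in numbers caught per trap-night, but nowhere is an absolute margin set.

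**The concern.** A margin of 50% relative to the reference arm, tested on within-pair ratios, is a test against a ratio of 1.5. The sample-size section does not say that it used that scale, and its result does not follow on that scale from the CV of 0.3 that it says was used.

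The reader is told that 80% power already contains a safety allowance, because 0.3 is larger than the 0.23 seen in previous data. If the planned test falls short of 80% at 0.3, the allowance is not there in the form claimed, and an equivalent product has a larger chance of an inconclusive result than the article states. The Background says that a recommendation for the product depends on a non-inferiority trial of this kind, so the stated power should be that of the test to be performed.

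**Working it through.** **Inputs.** From the article: reference mean 3.0, within-pair CV k = 0.3 (0.23 from previous data), y = 49 trap-nights per cluster (180 planned), 8 pairs, margin 50%. Assumed, because the article does not state them: true densities equal; one-sided 2.5%, with one-sided 5% as the range; Poisson variation of catches within a cluster.

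**Step 1. Reproduce the stated figure.** The matched-pair formula for rates, with 2 clusters added for matching, is

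c = 2 + (z_α + z_β)² × [(λ0 + λ1)/y + k²(λ0² + λ1²)] / d².

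Take d = 1.5 (50% of 3.0), λ0 = λ1 = 3.0, k = 0.3, y = 49, one-sided 2.5%:

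- (z_α + z_β)² = (1.960 + 0.842)² = 7.849
- bracket = 6/49 + 0.09 × 18 = 0.1224 + 1.62 = 1.7424
- c = 2 + 7.849 × 1.7424 / 2.25 = 8.08

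With 8 pairs the same formula gives 79.5% power. An exact noncentral paired t-test on the difference gives 78.7% (noncentrality 1.5/√(1.7424/8) = 3.214, 7 df). This matches the stated 8 clusters and 80%, at the stated CV.

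**Step 2. Power of the planned ratio test.** On the log scale, the variance of one pair's log ratio is 2(k² + 1/(3.0 × y)), and the margin is ln 1.5 = 0.4055.

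For k = 0.3 and y = 49: variance = 2(0.09 + 0.0068) = 0.1936; SE with 8 pairs = √(0.1936/8) = 0.1556; noncentrality = 0.4055/0.1556 = 2.606; 7 df.

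| CV | Trap-nights | Noncentrality | Power, one-sided 2.5% | Power, one-sided 5% |
|---|---|---|---|---|
| 0.30 | 49 | 2.606 | 61.1% | 75.8% |
| 0.30 | 180 | 2.676 | 63.3% | 77.7% |
| 0.23 | 49 | 3.319 | 81.1% | 90.9% |
| 0.23 | 180 | 3.466 | 84.3% | 92.8% |

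At CV 0.3 and 49 trap-nights, 80% on this scale would take 12 pairs at one-sided 2.5% or 9 at one-sided 5%.

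**Step 3. Where the gap comes from.** The variation is the same on both scales: 1.7424/3.0² = 0.1936, the log-ratio variance. Only the margin differs, 0.5 of the mean on the difference scale against ln 1.5 = 0.4055 on the log scale. The noncentrality falls in that proportion: 3.214 × 0.4055/0.5 = 2.606. The fixed margin of 1.5 also treats the reference mean as known.

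**Step 4. Does this rest on the log transformation?** Simulation with 100,000 trials per setting (8 pairs, CV 0.3, 49 trap-nights, lognormal or gamma cluster means, Poisson counts):

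| Test | One-sided 2.5% | One-sided 5% |
|---|---|---|
| Log ratio against ln 1.5 | 59–62% | 74–77% |
| Untransformed ratio against 1.5 | 53–57% | 64–67% |
| New minus 1.5 × reference, against 0 | 59–60% | 75–76% |
| Difference against a fixed 1.5 | 79% | 89% |

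All three forms of a relative 50% margin fall below 80% at both levels. Only the fixed absolute margin reaches about 80%.

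**The case against.** **The stated figure is reproducible.** This stands. With the article's own CV of 0.3 and a standard form of the cited method, 8 clusters and about 80% come out. A reader might infer that the authors really used 0.23, because two other set-ups give about 8 at that value: the formula with 3.0 and 4.5 in the variance (7.93 clusters) and the log-ratio t-test (81%). The document does not support that inference. Under the equal-rates calculation that matches at 0.3, a CV of 0.23 would give 5.75, so 6 clusters. Putting 4.5 in the variance (11.72 clusters at CV 0.3) also places the new product at the margin, whereas non-inferiority power is usually computed at equality.

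**The 61% rests on unstated choices.** It needs one-sided 2.5% and a log transformation, and the article states neither. At one-sided 5% the shortfall is about 4 points, or 2 with 180 trap-nights. That is fair, and is why both levels are shown; the sign of the result does not change with the level or the transformation.

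**Power may be better in practice.** Twenty baseline clusters are used to improve matching, the analysis adjusts for covariates, and previous data suggest a CV of 0.23, where the ratio test has 81% or more. This is a reason for some confidence in the design. It does not make the stated figure right for the planned test at CV 0.3. Catches more variable than Poisson would pull the other way.

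**The objective speaks of a difference.** It does, but with no absolute margin attached, and the analysis section specifies ratios.

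**Conclusion.** The concern holds as a mismatch of scale between the sample-size calculation and the primary analysis. At CV 0.3, 80% power belongs to a fixed margin of 1.5 mosquitoes per trap-night. The planned ratio test against 1.5 has about 61% at one-sided 2.5% or 76% at one-sided 5%, so a truly equivalent product would miss non-inferiority in about 39% or 24% of trials at that CV. It reaches 80% at CV 0.23.

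These figures assume equal true densities, a mean of 3.0, 49 trap-nights, Poisson variation within clusters and no gain from covariate adjustment. The shortfall at CV 0.3 holds at both usual levels and with 180 trap-nights. It is not shown that the wrong CV was entered, and nothing in the article suggests that a failed result would be read as proof of inferiority.

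**What to change.** In the sample-size section, state the significance level, its sidedness, and that the margin is a density ratio of 1.5. Replace the unqualified 80% at CV 0.3 with the power of the ratio test given under Data analysis, at the level the trial will use. For example: with 8 pairs, true ratio 1, ratio margin 1.5 and 49 trap-nights, power is 81% at CV 0.23 and 61% at CV 0.30 (one-sided 2.5%), or 91% and 76% (one-sided 5%). The corresponding figures for 180 trap-nights (84% and 63%, or 93% and 78%) can be added.

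If an absolute margin of 1.5 mosquitoes per trap-night was intended, the margin and the primary analysis would have to say so instead. No added clusters are needed. The only cost is a less favourable stated figure and a few sentences of text.
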